### **1.1.4. The eMind application**

Professionals from the addictology department at the CHU Dijon Bourgogne, trained in both addictology and Mindfulness, have created Mindfulness content that has been implemented on a digital platform in the form of an e-health application, called eMind. This implementation was made possible thanks to collaboration with public players such as the Agence Régionale de la Santé Bourgogne Franche Comté (ARS BFC) and the Groupement régional d'aide au développement de la e-santé (GRADeS). The latter are certified "Hébergeur de Données de Santé" (HDS) for all the following activities:

- The provision and maintenance in operational condition of physical sites to host the hardware infrastructure of the information system used to process health data;
- The provision and maintenance in operational condition of the hardware infrastructure of the information system used to process health data;
- Provision and maintenance in operational condition of the information system's application hosting platform;
- Provision and maintenance in operational condition of the virtual infrastructure of the information system used to process health data;
- Administration and operation of the information system containing health data;
- Health data backup.

The eMIND application includes weekly educational modules in the form of videos and audio exercises for daily practice. The application is intended for clinical use as a complement to standard treatment. As such, quality requirements such as data security, the scientific value of the information delivered, as well as ease of use or usability must apply.

The content of our application has been created by trained healthcare professionals, guaranteeing the quality of the information delivered. With regard to usability or ease of use, the French health authority (Haute Autorité de Santé) recommends that it be evaluated with the target population (10). A high level of usability is expected.

We propose to evaluate our original digital MBI by measuring the acceptability and usability of this e-health tool in a population of smokers undergoing smoking cessation with standard treatment. We will combine this with a partnership research approach involving patient participation, in order to co-construct the final version of the application.

## Research hypothesis

In this context, we formulate the hypothesis that, for our application to be optimally effective, taking into account the experience and expectations of the people concerned is one of the keys to better adherence to the application.

## Project originality and expected results

We propose a single-center, mixed-methods pilot study to assess the acceptability and usability of the eMind application in a population of smokers wishing to quit.

eMind is the first Mindfulness application for smoking cessation to enable patients to follow a complete 8-week MBI that recreates as closely as possible the conditions of a classic MBI. It differs from other Mindfulness applications in that most existing applications offer only elements of Mindfulness programs, without the rich, intensive and progressive training process of a standard 8-week program. Compared with a traditional face-to-face program, Mindfulness practice via eMind is said to encourage patients' autonomy in deciding when to practice, and to be more compatible with their life rhythms.

The eMind application will be co-constructed: it will be based on a partnership research approach with patient participation. A first version of the content has been created in the university hospital addictology department by healthcare professionals trained in mindfulness. This first version of the application - a beta version - will be modified according to patient feedback. To reward their contribution to the final version of the application, patients will be compensated in the form of a gift card. A session to present the results of the study and the new version of eMind will be organized once the modifications have been taken into account.

Knowledge of the acceptability and usability of the beta version of eMind, as well as a study of the motivations and obstacles to its use, will provide us with information on the needs of the participants in terms of the operation of the eMind application. This will make it easier to overcome any obstacles encountered, so as to achieve optimum involvement. These evaluations will enable us to make the necessary adjustments before rolling out the program on a larger scale.

Data on the effect size of our intervention will be used to calibrate a large-scale national intervention trial aimed at evaluating the effectiveness of the improved version of eMind, thanks to feedback from participants in the HowToMind study, as part of the participatory research approach.

Our application could offer new therapeutic perspectives for smokers. This treatment could benefit the 12.2 million smokers in France (1 billion smokers worldwide). It is therefore crucial to guarantee the usability of our application, so that we can later explore its efficacy in a large multicenter randomized controlled trial

In terms of public health gains, even a small effect would be significant given the prevalence of smokers in the French population. For example, if the minimum detectable effect were achieved for eMind, the 1-year abstinence rate after smoking cessation would rise from 16% to 25%. Given that almost 25% of smokers have tried to quit in the past year, and that 27% of the population aged 18 to 75 currently smoke, this means that around 300,000 more smokers will maintain their abstinence each year if this application is widely available (17).

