| Experimental design | We propose a single-center mixed pilot study of the usability and adherence to the eMind application - beta version - in a population of smokers wishing to stop smoking.  Participants will have access to the eMind application to follow the 8-week MBI smoking cessation program. At the same time, they will receive a standard treatment combining nicotine patches and lozenges. |
| Objectives | - Main objective:   Evaluate the acceptability and usability of the eMind application, at 8 weeks, among smokers wishing to stop smoking. In addition, a qualitative component (focus groups) is planned to gather their feedback, their expectations and the determinants of the application's acceptability.   - Secondary objectives:   Study changes in tobacco consumption between inclusion and last follow-up (6 months).  Study the impact of eMind on smoking at 3 and 6 months after inclusion  Study the evolution of craving between inclusion and the last visit (12 weeks).  To evaluate the tolerance of smoking cessation accompanied by the eMind application .  Study the evolution of mindfulness practice at 3 and 6 months. |

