## Secondary objectives

Study changes in tobacco consumption between inclusion and last follow-up (6 months).

Study the impact of eMind on smoking at 3 and 6 months after inclusion.

Study the evolution of craving between inclusion and the last visit (12 weeks).

Evaluate the tolerance of smoking cessation supported by the eMind application.

Study the evolution of mindfulness practice at 3 and 6 months.

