# METHODOLOGY

## Study diagram

We propose a single-center pilot study to characterize the acceptability and usability of the beta version of the eMind application among smokers. The effect size of this intervention on the maintenance of smoking abstinence will be collected as a secondary endpoint.

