## Calculating the number of subjects required

### **Justification**

We will include 60 patients (N = 60). The number is based on the sample size commonly used in pilot studies. In addition, we are planning three different focus groups with 6 to 8 participants in each. Given the potential for some participants to be lost to follow-up and unavailable to participate in focus groups, N = 60 seems to us to fit in well with the chosen methodology

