## Associated treatments

Participants in this study will receive NRT in transdermal (patch) and oral (lozenge) forms, which is a standard treatment in this indication. The evolution of NRT doses will depend on the patient's clinical assessment, thus reproducing real NRT treatment conditions. The nicotine patch is applied to dry skin every 24 hours. Lozenges will be used as needed, up to 10 lozenges per day.

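### The protocol promises an effect size and an impact of eMind on smoking, but with no comparator it can only describe uncontrolled outcomes under eMind plus NRT

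*Protocol*

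**What the plan says.** Three statements claim an effect of the application.

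- Protocol section 1.3, repeated in the synopsis under expected results: "Data on the effect size of our intervention will be used to calibrate a large-scale national intervention trial".
- Section 4.1: "The effect size of this intervention on the maintenance of smoking abstinence will be collected as a secondary endpoint".
- Section 2.2, repeated in the synopsis objectives: "Study the impact of eMind on smoking at 3 and 6 months after inclusion".

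The design is given in the same document. Section 4.1 describes it thus: "We propose a single-center pilot study to characterize the acceptability and usability of the beta version of the eMind application among smokers". On exposure to the application, the synopsis (experimental design) says: "Participants will have access to the eMind application to follow the 8-week MBI smoking cessation program". On background treatment, section 5.2 says: "Participants in this study will receive NRT in transdermal (patch) and oral (lozenge) forms, which is a standard treatment in this indication". Motivation to quit is an inclusion criterion (section 4.3.1). Participants attend the addictology department at inclusion and at weeks 4, 8 and 12 (sections 6.3 and 6.4), and the principal investigator may contact those who leave the calendar or craving scale unfilled (section 5.1). No control group, randomisation, historical control or benchmark appears anywhere. Section 10.1 makes the secondary analyses descriptive or exploratory, and section 10.3 rules out tests.

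**The concern.** An effect of eMind is a contrast between outcomes with the application and outcomes without it under otherwise equal care. Only the first half of that contrast is observed here. Abstinence at 3 or 6 months, or the fall in consumption from baseline, also contains whatever is due to patches and lozenges, the visits, the participants' own decision to stop and the ordinary course after enrolment. Section 1.1.2 itself presents NRT as an effective treatment, so on the protocol's own account the background is active.

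At stake are two things. One stated objective and one stated secondary endpoint cannot be estimated as worded. And a figure that may owe much of its size to NRT and clinic support could be carried forward, under the label of effect size, into a randomised trial that needs a between-arm difference.

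**Working it through.** **Is there a plan figure to reproduce?** No. The sample size of 60 has no power or precision target behind it; section 4.2.1 says "The number is based on the sample size commonly used in pilot studies" and adds focus-group needs and losses to follow-up. No effect measure is defined: the secondary endpoints in section 3.2 are consumption, CO, 7-day abstinence, craving, mindfulness practice and symptoms.

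**What the data identify.** Let p1 be the abstinence proportion under eMind plus NRT plus visits in motivated smokers, and p0 the proportion in the same people and care without eMind.

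- Effect of eMind = p1 − p0 (or p1 / p0 as a relative risk).
- This study estimates p1 only. Nobody is observed without eMind, and no value of p0 is specified.
- The same holds for change from baseline: the observed mean change is the change under the whole package, and the change without eMind is not observed.

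**Illustration (assumed result, not a prediction).** Suppose 15 of 60 are abstinent, so p1 = 15/60 = 25%.

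Exact (Clopper-Pearson) 95% CI:

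- lower limit = 2.5% quantile of Beta(15, 46) = 14.7%
- upper limit = 97.5% quantile of Beta(16, 45) = 37.9%

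The protocol mentions two background figures: 15–25% at 6 months among smokers who have quit (section 1.1.2), and 16% at 1 year (section 1.3). Putting values from them in the place of p0:

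| assumed p0 | p1 − p0 | p1 / p0 |
|---|---|---|
| 15% | 25 − 15 = +10 points | 25/15 = 1.67 |
| 16% | 25 − 16 = +9 points | 25/16 = 1.56 |
| 20% | 25 − 20 = +5 points | 25/20 = 1.25 |
| 25% | 25 − 25 = 0 points | 25/25 = 1.00 |

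One and the same observed result is thus a 10-point benefit or none, according to a number that the study does not produce. Neither figure is a matched control rate. The first concerns people who had already quit. The second is a 1-year rate, while this study measures 7-day abstinence at visits up to week 12 and consumption by telephone at 6 months. The table shows only that p0 is missing; it does not estimate the effect.

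**Two separate issues.** The width of the interval is imprecision at N = 60, and a larger sample would narrow it. The missing p0 would remain at any sample size. The second is the point made here.

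**A further mismatch.** Section 1.3 says that the national trial will evaluate the improved application, whereas this study observes the beta version.

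**The case against.** The case for leaving the text alone has real substance.

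- **The core of the study does not rest on it.** The primary objective is acceptability and usability at 8 weeks. Its analyses are the MARS-F mean and the user-category percentages with confidence intervals, and N = 60 comes from pilot convention and focus groups. This stands, and it limits the seriousness of the point.
- **The analysis plan is modest.** Secondary analyses are descriptive or exploratory, no test is made, and section 1.3 defers efficacy to a later randomised trial. This too stands, but an exploratory analysis cannot supply a contrast that the data lack. The mismatch between that modest plan and the wording of sections 1.3, 2.2 and 4.1 is the fault.
- **The intervention may mean the package.** Section 5.1 describes eMind as given on top of standard treatment, and uncontrolled change under that package can be estimated. That softens sections 1.3 and 4.1. It does not rescue section 2.2, which names eMind alone.
- **The endpoint list does not contain an effect size.** True of section 3.2; the claim is one sentence in section 4.1. It is still a statement of what will be collected.

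A reader might go further and infer that the national trial will be wrongly sized. The document does not establish this: it speaks of calibration, never of sample size or power, and section 1.3 already mentions a minimum detectable effect (16% to 25% at 1 year). A reader might also infer that the pilot can offer nothing beyond feasibility counts. That is too strong as well, because abstinence under eMind plus NRT is a legitimate planning input.

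**Conclusion.** The point holds as a should-fix. As written, the protocol attributes to this study an effect size and an impact of eMind that its design cannot give. What it can give is an uncontrolled abstinence proportion and an uncontrolled within-person change under eMind, NRT and specialist follow-up together.

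This rests on the reading that all participants receive eMind and NRT and that no comparator or reference value exists; the protocol does not use the term single-arm, but every description of exposure implies it. No numerical size can be put on the bias, because the quantity needed for that is the one missing. The 15/60 result is assumed, and the 15–25% and 16% rates are unmatched, so the figures above are illustrative only. The primary objective, its analyses and the sample size are unaffected.

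**What to change.** In sections 1.3, 2.2 and 4.1 and the matching synopsis rows, replace the references to an effect size and to the impact of eMind with wording such as: *abstinence proportion (with exact 95% CI) and change in tobacco consumption under eMind plus NRT, uncontrolled and not attributable to eMind*.

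Restate the calibration sentence in section 1.3 and the synopsis to say that the pilot supplies planning inputs for the later randomised trial (abstinence proportion under eMind plus NRT, retention, use of the application, completeness of outcomes, variability of consumption) and does not supply the between-arm effect. How that trial chooses its target difference and control rate can be left to its own protocol.

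The cost is wording only: no change to visits, data collection, sample size or the primary analysis. The downside is a less ambitious stated output.

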# OBJECTIVES

## Primary objective

Evaluate the acceptability and usability of the eMind application, at 8 weeks, among smokers wishing to stop smoking. In addition, a qualitative component (focus groups) is planned to gather their feedback, their expectations and the determinants of the application's acceptability.

## Secondary objectives

Study changes in tobacco consumption between inclusion and last follow-up (6 months).

Study the impact of eMind on smoking at 3 and 6 months after inclusion.

Study the evolution of craving between inclusion and the last visit (12 weeks).

Evaluate the tolerance of smoking cessation supported by the eMind application.

Study the evolution of mindfulness practice at 3 and 6 months.

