## Secondary endpoints s

The evolution of tobacco consumption between inclusion and 4 weeks, 8 weeks and 12 weeks will be measured using an electronic consumption calendar implemented in our application. A CO test will be performed at inclusion, 4 weeks, 8 weeks and 12 weeks. Smoking abstinence will be defined as the absence of tobacco consumption for 7 days prior to the assessment visit. A recent consensus of experts has recommended the use of 7-day punctual abstinence as an endpoint, as it is less affected by recall bias and missing data than continuous abstinence (16).

Assessment of tobacco consumption at 6 months, during a telephone call.

Craving intensity will be measured at baseline, 4 weeks, 8 weeks and 12 weeks using a visual analog scale (VAS) implemented in the application.

The evolution of mindfulness practice between inclusion and 4 weeks, 8 weeks, 12 weeks will be measured using an electronic consumption calendar implemented in our application.

Evaluation of mindfulness practice at 6 months, during a telephone call.

Symptoms related to smoking cessation (cravings, difficulty concentrating, headaches, irritability, fatigue, hunger, constipation), use of nicotine replacement therapy (skin irritation, abdominal pain, hiccups, gastroesophageal reflux, sleep disorders, nausea, diarrhea, dizziness) or MBI will be collected throughout the study.

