# INTERVENTION

## Study intervention

The study consists of the following two phases:

1. Supported learning phase (8 weeks) :

This phase will consist of Mindfulness training via the beta version of the eMind smartphone application, in addition to the standard treatment (TSN). The eMind application contains 8 thematic modules linked to both Mindfulness training and tobacco consumption (one module per week). Tools for daily practice will be available in audio/video and text formats (PDF documents). For each module, key messages will be delivered through a weekly video, and Mindfulness sessions ranging from 5 to 15 minutes each, available for daily practice (body scan, movement, breathing, etc.). The modules will target specific elements of addiction such as craving and automatic behavior, as well as transdiagnostic elements such as emotion, self-judgment and acceptance.

During this phase, each week a new module will be made available to the participant. Previously delivered modules will remain available for consultation at the patient's convenience.

*Summary of topics covered by the 8 learning modules :*

- Week 1: Introduction to Mindfulness
- Week 2: Addiction and automatic behavior
- Week 3: Craving
- Week 4: Emotion
- Week 5: Shame and judgment
- Week 6: Acceptance
- Week 7: Relapse
- Week 8: Building your practice

1. Independent practice phase :

The eMind application is designed to help participants acquire the skills they need to practice Mindfulness independently. Therefore, after the 8-week learning period, no new modules will be made available to participants. However, participants will be able to access all eMind resources as part of their autonomous practice

The smoking schedule (0 = no smoking, 1 = 1 cigarette, etc.; daily fill-in) and a craving assessment tool (VAS between 0 and 10; weekly fill-in) will also be implemented in the application. Similarly, the mindfulness practice calendar will be collected via the app (Do you practice mindfulness today: YES/NO, daily fill-in). In the event of non-completion of the calendar or the craving VAS, the principal investigator will receive alerts and will be able to contact the participant to offer help in the event of difficulties.

Through the eMIND application, two other types of alert will be set up:

- Patient reminders if video content is not viewed
- Alerts on the clinician interface in the event of non-viewing of video content by the patient.

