## End of study

Telephone call 6 months after inclusion, during which the following information will be collected:

- Tobacco consumption at 6 months
- A compendium of mindfulness practice

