## Technical description of measured parameters

- Tobacco consumption calendar, rated 0 = no consumption, 1 = 1 cigarette, etc., integrated into the eMind application: daily completion by the patient (with reminder notification).
- EVA Visual Analog Scale ("craving") rated from 1 to 10, integrated into the eMind application: weekly completion by the patient (with reminder notification).
- MARS-F Mobile Application Evaluation Scale composed of 23 items scored from 1 to 5 and exploring four objective domains (engagement, functionality, aesthetics, information quality) leading to a score between 0 and 95 and a 20-point subjective domain: collected at each visit by the investigator [15].
- Mindfulness practice calendar, integrated into the eMind application: daily completion by the patient (with reminder notification).

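### Any change in mindfulness practice up to 6 months cannot be separated from the switch from a daily app calendar to a telephone call

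*Protocol*

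**What the plan says.** Protocol section 2.2 lists the objective "Study the evolution of mindfulness practice at 3 and 6 months".

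For the period to week 12, section 3.2 places the measure in the app: "The evolution of mindfulness practice between inclusion and 4 weeks, 8 weeks, 12 weeks will be measured using an electronic consumption calendar implemented in our". Section 5.1 gives the item as "Do you practice mindfulness today: YES/NO, daily fill-in". Section 6.7 adds that the participant is reminded to complete it. Section 5.1 adds a second layer of follow-up: "In the event of non-completion of the calendar or the craving VAS, the principal investigator will receive alerts", after which the participant may be contacted.

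For 6 months, section 3.2 has a separate line: "Evaluation of mindfulness practice at 6 months, during a telephone call". Section 6.5 describes the content of that call on this point only as "A compendium of mindfulness practice".

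The procedures listed for Visit 4 (week 12) in section 6.4 are the consumption calendar, CO, craving, withdrawal symptoms and NRT use. They include no verbal question on mindfulness practice. The chart in section 6.11.2 nevertheless carries practice on a single row from Visit 1 to the 6-month call.

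**The concern.** The objective asks how practice evolves and names 3 and 6 months. The 3-month value and everything before it come from one method, and the 6-month value comes from another. The methods differ in mode (self-entry in an app against an interview by study staff) and in prompting (daily reminders and investigator alerts against one call). They probably also differ in recall, since one call about practice at 6 months must rely on memory to some degree.

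They may also differ in whom they capture. The calendar sits inside the app. Section 3.1 defines a group who no longer use the app after 8 weeks, and these participants may leave few calendar entries at week 12 even if they still practise without it. The telephone call could reach them at 6 months.

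What is at stake is the description of whether practice lasts beyond the first 12 weeks. The protocol itself takes recall seriously elsewhere: it times the focus groups to limit memory bias (section 6.4) and prefers 7-day abstinence partly because it is less prone to recall bias (section 3.2). The 6-month practice item has no such safeguard.

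**Working it through.** The document states no figure for this objective, so there is none to reproduce. The check is mainly a comparison of the method at each time point.

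| Time point | Method assigned in section 3.2 | Form of the item |
| --- | --- | --- |
| Weeks 4, 8 and 12 | App calendar | Daily YES/NO, with reminders and non-completion alerts (5.1, 6.7) |
| 6 months | Telephone call | Not specified (6.5) |

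1. Weeks 4, 8 and 12 share one method. Changes among them have no switch of instrument.
2. The 6-month value has its own method. Whether the change is taken from inclusion or from week 12, it crosses the switch.
3. No overlap is planned. Section 6.4 has no verbal practice question at Visit 4, and section 3.2 assigns no calendar window to 6 months.
4. With method and time fully aligned across that step, no later analysis can separate the two. The data needed for a bridge would not have been collected.

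**Illustration on assumed values.** None of these inputs is in the protocol.

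- True practice is constant at 4 days a week.
- *c* is the share of practice days entered in the calendar, from 0.6 to 1.0, with blank days counted as no practice.
- *o* is the telephone reporting factor, from 1.0 to 1.25.

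Apparent change = 4 × *o* − 4 × *c*.

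- *c* = 1.0, *o* = 1.0: 4.0 − 4.0 = 0
- *c* = 0.8, *o* = 1.0: 4.0 − 3.2 = +0.8 days a week
- *c* = 0.8, *o* = 1.25: 5.0 − 3.2 = +1.8 days a week
- *c* = 0.6, *o* = 1.25: 5.0 − 2.4 = +2.6 days a week

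The sign follows *o* − *c*. The assumed ranges keep *o* at or above *c*, so the result cannot be negative here. If participants under-reported by telephone so that *o* fell below *c*, the same formula would show a decline with no change in behaviour. If blank days were left out instead of counted as no practice, the calendar term would change as well. The illustration shows that the method can move the result; it does not estimate by how much.

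**The case against.** The strongest reply is that the protocol does not define a change from week 12 to 6 months. Section 3.2 attaches the word evolution to the calendar up to week 12 and calls the 6-month item an evaluation. It is true that no change score is defined. But section 2.2 places both time points under one objective on evolution, and the chart in section 6.11.2 treats practice as one variable through to 6 months. A reader of the results will compare the two values unless told not to.

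Second, a reader might infer that a true decline will be disguised as maintenance, because missed calendar days pull the earlier value down and telephone answers are inflated. The document does not support that. The item is an explicit YES/NO, so a blank can be told apart from a NO; nothing says blanks count as NO; and reminders and alerts should reduce them. Over-reporting by telephone is an assumption.

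Third, a reader might infer that the call uses a different unit and a long recall period. The protocol gives neither. The wording of section 6.5 looks like a translation, and the call could ask for days practised. This stands as a limit on the claim. Even a matched unit, however, would leave mode and prompting different, with no overlap to measure their effect.

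Fourth, a reader might infer that the plan says nothing about practice after the supported phase, or that the calendar stops at week 12. Neither follows. After week 8, "participants will be able to access all eMind resources as part of their autonomous practice", and weeks 8 to 12 are covered by the calendar alone. Section 7.3 gives no end date for collection in the app. What remains is that section 3.2 assigns the 6-month endpoint to the call and plans no calendar measure beside it.

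Finally, the share of follow-up days covered by the calendar is no measure of bias: assessments at 3 and 6 months do not need daily coverage in between.

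**Conclusion.** The point holds in a limited form. The 6-month value comes from a different method from all earlier values, and no time point is measured both ways. A change in practice to 6 months is therefore not interpretable as a change in behaviour.

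Neither the direction nor the size of the distortion can be determined from the document. The range of 0 to +2.6 days a week holds only under the assumptions shown.

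The severity is minor. The endpoint is secondary, section 10.1 makes secondary analyses descriptive or exploratory, and section 10.3 plans no test, so no error rate is affected. The primary results at 8 weeks do not depend on it. The point is still worth raising because the gap lies in data collection and cannot be filled afterwards.

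**What to change.** In sections 6.4 and 6.5, add one identically worded question with a fixed recall window, asked at Visit 4 and at the 6-month call. An example is the number of the last 7 days on which the participant practised mindfulness, with or without the app. Base the 3-versus-6-month description on that question alone.

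Keep the calendar for the trend to week 12. Report the Visit 4 difference between the calendar and the verbal answer over the same 7 days, so that readers can see how far the methods disagree. State that no direct calendar-to-phone change will be computed.

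The cost is one extra question at an existing visit and a fixed wording for an existing call. The drawback is that a 7-day verbal answer is cruder than a daily calendar. The question needs to be in place before participants reach Visit 4. For anyone already past it, report the 6-month value on its own, without a change from 3 months.
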